#### Secondary criteria

The number of self-extubations, repositioning of the ETT will be estimated and compared using a Poisson regression model taking into account the study design. An offset of the logarithm of the intubation time will be included in the model.

The time to the first peri-oral lesion will be estimated using a random-effects survival model to account for the study design.

The time to onset will be calculated from the date of intubation to the date of first lesion onset. Patients for whom no lesion appeared will be censored at the date of extubation or at the date of discharge from intensive care or at D28. Patients who died will be censored at their date of death.

The grade of skin lesions (NPUAP scale) and mucosal lesions (Rompis scale) will be collected for each lesion. If the patient has no lesions, a grade=0 on the corresponding scale will be retained. If a patient presents several lesions, the maximum grade observed will be retained.

An ordinal logistic regression model controlling for intubation time and study design will be applied to compare both types of fixation.

The incidence of peri-oral lesions (expressed per 1000 ventilator days) will be calculated and described in each group: number of patients with at least one lesion / total number of ventilator days (up to 1ère lesions in patients with one lesion)

The maximum number of injuries per day will be estimated and compared using a linear model taking into account the study design.

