### **2.2.2. Secondary endpoint(s)**

- Number of self-extubations
- Number of significant repositioning of the endotracheal tube performed following a movement of more than 2 cm from the initially set marker.
- Time to the first peri-oral lesion from the time the patient is intubated until extubation.
- Assessment of the grade of cutaneous peri-oral lesions by the NPUAP scale.  
If several lesions co-exist, the lesion with the most severe grade will be retained.
- Evaluation of the intensity of the mucosal peri-oral lesions by the ROMPIS scale. If several lesions co-exist, the lesion with the most severe grade will be retained.
- Number of patients with at least one peri-oral lesion per 1000 ventilation days
- Maximum number of lesions per day

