### **Analysis of the assessment criteria**

To account for the study design, all criteria (primary and secondary) will be compared using hierarchical generalized linear models. The type of fixation, the period and the center (=cluster) will be taken into account in the model as fixed effects; the center\*period interaction will be taken into account as a random effect (14).

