### **6.2.2. Statistical justification of the number of inclusions**

The study will take place in 16 centers (clusters) over two 12-month periods.

According to the IDEFIX study (7), we hypothesize that 35% of patients with a "cord and sleeve" fixation system have a peri-oral lesion compared to 20% with the elastic adhesive tape system.

The calculation of the number of subjects needed must take into account the design of the study and thus the two intra-class and inter-class correlation coefficients (15)

As we have no data on the estimation of correlation coefficients, we have retained, for the calculation of the number of subjects, a "moderate" intra-class correlation coefficient and therefore defined at 0.1, and as recommended, an inter-class correlation coefficient equal to half of the intra-class correlation coefficient, i.e. 0.05 (16)

With 90% power and 5% alpha risk, we calculated that each of the 16 centers would need to include an average of 24 patients per period.

A total of 768 patients are to be included.

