### **6.2.3. Expected level of statistical significance**

The alpha risk is set at 5%.

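### The Poisson mixed model for tube repositionings lacks a small-sample correction: with 18 mean parameters on 32 centre-periods, an ordinary maximum-likelihood fit would test at about 15-22% instead of 5% if counts are overdispersed.

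*Protocol*

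**What the plan says.** Section 2.2.2 of the protocol lists as secondary endpoints the number of self-extubations and the "Number of significant repositioning of the endotracheal tube" after a movement of more than 2 cm. Both are counts per patient, followed to extubation or D28 (section 2.2.1).

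Section 6.2.1 (Secondary criteria) says that these counts will be "compared using a Poisson regression model taking into account the study design", with the logarithm of intubation time as an offset. The design terms are set just before, for all criteria: "The type of fixation, the period and the center (=cluster) will be taken into account in the model as fixed effects", with the centre-by-period interaction as a random effect.

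Section 6.2.3 sets alpha at 5%. Section 6.2 names R 3.5.1 as the software. The estimation method, the reference distribution for the test and any handling of overdispersion are not stated.

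**The concern.** Repositionings can recur in one patient over many intubated days, so the variance between patients will probably exceed the Poisson variance. The only term in the stated model that can take up the excess is the random centre-by-period effect. Its variance must be estimated from 32 cells after 18 mean parameters have been fitted. If that estimate is too low, the standard error of the fixation effect is too small and the test too liberal.

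Section 2.2.1 makes repositioning one of two criteria for whether the device holds the tube, and the trial aims to harmonise practice. A spurious difference in tube security, in either direction, could colour the advice drawn from the lesion result.

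**Working it through.** **1. The plan's own figure.** The protocol gives a sample size for the primary endpoint only (section 6.2.2): 35% versus 20%, 90% power, 5% alpha (two-sided assumed), within-period correlation 0.10, between-period correlation 0.05.

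- Patients per arm without clustering: (1.960 + 1.282)² × (0.35×0.65 + 0.20×0.80) / 0.15² = 180.96.
- Design effect: 1 + (m − 1)×0.10 − m×0.05 = 0.90 + 0.05m.
- Solve 16m = 180.96 × (0.90 + 0.05m): m = 23.4, rounded up to 24. Total 16 × 2 × 24 = 768, as stated.

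This confirms the layout used below: 16 centres, 2 periods, 24 patients per cell. The protocol gives no comparable figure for the count endpoints.

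**2. What the model works with.** Section 6.2.8 gives each centre one fixation per period. Fixation, period and centre are therefore constant within a centre-period. The patient-level Poisson mixed-model likelihood then equals that of the 32 cell totals up to a constant. This was checked numerically: at three parameter settings the two log-likelihoods differed by the same constant, to four decimals. Variation between patients beyond Poisson reaches the model only as extra variation between cells, which the random effect can represent.

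**3. Degrees of freedom.** Mean parameters: 16 centres + 1 period + 1 fixation = 18. Residual: 32 − 18 = 14. Maximum likelihood divides by 32 rather than 14, so when variation between cells dominates, the standard error is scaled by √(14/32) = 0.66. The limiting type I error of a 1.96 test is P(|t₁₄| > 1.96 × 0.661) = P(|t₁₄| > 1.296) = 21.6%. A t reference without correcting the standard error would still give P(|t₁₄| > 2.145 × 0.661) = 17.8%.

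**4. Simulation with no fixation effect.** Assumptions: centre SD 0.4 on the log scale, intubation 2 to 28 days with mean about 8.3 (section 1.1 gives an average of 7 to 10), gamma variation between patients, maximum likelihood by adaptive quadrature. Runs: 2000 per scenario for the first two result columns, 4000 for the last. Monte Carlo standard error is about 0.9 points near 20%. Repositioning rate and dispersion are assumed, because the protocol gives neither. Self-extubation rates follow the 7-16% of patients in section 5.2.2, which also counts accidental extubations.

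| Events per patient | Patient variance | Centre-period SD | No random effect | Planned model (z) | Centre-level t, 14 df |
|---|---|---|---|---|---|
| 3 | 0 | 0 | 6.1% | 6.1% | not run |
| 1 | 0 | 0.2 | 17.0% | 15.5% | not run |
| 3 | 0 | 0.2 | 33.5% | 21.0% | not run |
| 1 | 0.5 | 0 | 15.7% | 14.5% | not run |
| 3 | 0.5 | 0 | 28.5% | 20.2% | not run |
| 1 | 1 | 0 | 23.3% | 19.4% | 4.3% |
| 3 | 1 | 0 | 43.4% | 22.0% | 4.8% |
| 3 | 2 | 0 | 55.0% | 22.1% | 4.9% |
| 3 | 1 | 0.2 | 51.2% | 22.1% | 5.2% |
| 0.07 | 0.5 to 1 | 0 | 4.8-5.8% | 4.8-5.8% | not run |
| 0.16 | 0.5 to 1 | 0 | 5.8-7.6% | 5.7-7.6% | not run |

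Likelihood-ratio tests of the planned model are within about 2 points of the z column. The mean standard error over the empirical SD is 0.064/0.099 = 0.65 (3 events, variance 1), 0.080/0.120 = 0.67 (1 event, variance 1) and 0.055/0.083 = 0.66 (3 events, variance 0, SD 0.2), close to the 0.66 of step 3. Two smaller runs with separate code, at 3 events and variance 1, gave 20.4% (250 trials) and 22.5% (200 trials).

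**5. Negative binomial with the same design terms** (likelihood-ratio test, 400 runs each). With no true centre-period variance: 3.0-6.2%. With centre-period SD 0.2 and patient variance 1: 8.7% (1 event) and 10.2% (3 events). At 3 events and variance 1, SD 0.3 gives 16% and SD 0.4 gives 23%.

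**The case against.** **The random effect does its job.** A reader might infer that repeat events go unmodelled because the random centre-by-period effect does not absorb them. The documents do not support that. Fixation varies only at the level of that effect, so the effect takes up most of the excess: at 3 events per patient, rejection falls from 43-55% without it to 22% with it. What remains is a matter of estimation and degrees of freedom. It appears equally with no patient overdispersion when centre-periods differ (21.0% at SD 0.2). This part of the objection stands and decides the remedy.

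**Self-extubations.** A reader might also infer that both count endpoints are far too liberal. At the protocol's own frequency the rate is about 5-8%, and about 10% only in an extreme case (0.12 per patient, variance 2). The strong statement is confined to repositioning.

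**The analysis plan may settle it.** The fitting method, reference distribution and dispersion checks are often left to the statistical analysis plan, which is not at hand, and the protocol cites a methods paper for its design terms. So the size is conditional on an ordinary maximum-likelihood fit. But the protocol itself names the Poisson family and every fixed and random term, and those choices leave 14 degrees of freedom. A routine fit of what is written has the problem.

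**Consequences.** These are secondary endpoints. The safety committee sees descriptive data without tests (section 5.6), so its work is unaffected. This limits the importance of the point.

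**Conclusion.** The concern holds for the repositioning count. If repositionings are overdispersed between patients, or their rates differ between centre-periods, an ordinary maximum-likelihood fit of the stated model rejects in about 15-22% of null trials at a nominal 5%, with a standard error up to about one third too small. The ceiling near 22% follows from 18 parameters on 32 cells and hardly depends on the simulation settings. Where in the range the trial would fall depends on assumed rates (1 to 3 per patient), an assumed gamma variance (0.5 to 2) or an assumed centre-period SD (0.2). If there is neither overdispersion nor centre-period variation, the planned model is close to nominal (6.1%). Variation between periods within a centre is not remote: for the primary endpoint the protocol itself plans with a within-period correlation of 0.10 and "an inter-class correlation coefficient equal to half of the intra-class correlation coefficient, i.e. 0.05". The point merits correction, but it does not touch the primary result.

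**What to change.** In section 6.2.1 (Secondary criteria), replace the Poisson comparison of repositionings with a centre-level analysis. For each centre, take the difference in log rate (events over intubation days) between period 2 and period 1. Compare the mean difference of the 8 centres in one sequence with that of the 8 in the other, using a pooled two-sample t test on 8 + 8 − 2 = 14 degrees of freedom. Half the difference between sequences estimates the log rate ratio for fixation.

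Alternatively, keep the mixed model and state an equivalent small-sample correction, such as REML-type estimation with 14 degrees of freedom. A t reference added to an uncorrected standard error is not enough (17.8% in the limit). A negative binomial model can be reported in addition, but not as the only remedy.

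For self-extubations the need is weaker. At 7-16% of patients a cell of 24 expects only 24 × 0.07 = 1.7 to 24 × 0.16 = 3.8 events, so log rates would need a small constant for empty cells (0.5 was used in the check above), and the corrected mixed model may be more practical.

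Cost: one sentence and no new data. Where excess variation is present, intervals widen by up to 2.145 / (1.96 × 0.661) ≈ 1.65 times relative to the uncorrected fit, most of which restores the correct standard error. Power on this secondary criterion falls somewhat.

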### **2.2. SECONDARY OBJECTIVES AND EVALUATION CRITERIA**

#### **2.2.1. Secondary Objective(s)**

- Verify the effectiveness of the device in maintaining the endotracheal tube in terms of self-extubation from intubation until extubation or D28.
- Verify the effectiveness of the device in maintaining the endotracheal tube in terms of repositioning the tube from intubation until extubation or D28.
- Compare the time to the first peri-oral lesion from intubation to extubation or D28.
- Compare the intensity of peri-oral skin lesions assessed by nurses from intubation till extubation or D28.
- Compare the intensity of mucosal peri-oral lesions assessed by nurses from intubation till extubation or D28.

- Assessing the incidence of peri-oral lesions
- Evaluate the impact of the intervention on the maximum number of lesions per day.

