### **Inclusion**

This trial relates to care practice. In order to meet the main objective, it requires homogeneity of intubation fixation practices within a given department during each of both inclusion periods, regardless of the status of the patient in the study (included or not).

Thus, in each ICU participating in the project, whatever the inclusion arm considered (A or B), all patients requiring invasive mechanical ventilation (MV) from their admission to the intensive care unit (if the respiratory assistance was set up before admission to the intensive care unit) or from the moment the respiratory assistance was set up (if it was set up in the intensive care unit), will benefit from the fixation method according to the inclusion arm (A or B) described above, whether they are included in the study or not. D0 is defined as the first day of the study fixation system of the ETT (cord + sheath or elastic adhesive bands).

Information and consent to participate in the study will be sought from patients requiring MV (or their relatives), who meet all the inclusion criteria and have no non-inclusion criteria (see chapter 3.3).

In the absence of the physical presence of the trusted support person or a relative, an emergency procedure will be available to include the patient. In all cases, the relative and then the patient will be informed as soon as possible by the investigator who will deliver the information note and the collection of their oral consent will be carried out secondarily by the investigator.

After having ensured the consent of the patient or his relatives or having followed the emergency inclusion procedure, the investigator can then include the patient before the D1 photograph. Moreover, if the information was initially given to the relatives, the consent will also be sought from the patient as soon as his level of vigilance allows it.

One of the criteria for non-inclusion of the patient is the presence of pre-existing facial lesions on arrival in the ICU in the path of the endotracheal tube fixation.

When the patient is admitted to the ICU already intubated, the tube is already fixed and this fixation is generally changed in order to put in place the fixation system used in the department. Within the framework of the protocol, we will ask that it be systematically changed to install the fixation system under study. The non-inclusion criterion can therefore be assessed at this point.

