## FIXATUB protocol

- the average duration of ventilation for patients who require invasive respiratory assistance for more than 48 hours
- risk factors for pressure ulcers which are essentially present at the beginning of the management of patients in shock (oedema, sedation, decrease in tissue perfusion, undernutrition, vasopressor treatments)

The follow-up by the nurse's notebook will stop at the final extubation or at the discharge from the ICU if the patient is discharged intubated from the ICU before D28 or at most D28.

|                              |
|------------------------------|
| SCHEDULE OF THE STUDY |
|------------------------------|

| Actions                                                                                             | D0 | D1 | D2 | D3 | D4 | D5 | D6 | D7 | D8 | D9 | D10 | D22 to D27 | D28 |
|-----------------------------------------------------------------------------------------------------|----|----|----|----|----|----|----|----|----|----|-----|------------|-----|
| Inclusion / non-inclusion criteria                                                                  | X  |    |    |    |    |    |    |    |    |    |     |            |     |
| Participation agreement                                                                             | X  |    |    |    |    |    |    |    |    |    |     |            |     |
| Biological assessment for SOFA                                                                      | X  |    |    |    |    |    |    |    |    |    |     |            |     |
| Assessment of peri-oral lesions:                                                             |    |    |    |    |    |    |    |    |    |    |     |            |     |
| ▮ Paramedical examination (peri-oral lesion survey)                                                 | X  | X  | X  | X  | X  | X  | X  | X  | X  | X  | X   | X          | X   |
| ▮ Photographs (during the change of the fixation system)                                            | X  | X  | X  | X  | X  | X  | X  | X  | X  | X  | X   |            |     |
| Collection of endotracheal tube mobilizations                                                       | X  | X  | X  | X  | X  | X  | X  | X  | X  | X  | X   | X          | X   |
| Collection of the repositioning of the endotracheal tube                                            | X  | X  | X  | X  | X  | X  | X  | X  | X  | X  | X   | X          | X   |

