### 5.2.2. Adverse events / Expected incidents

- List of Incidents/Expected Events related to the investigational medical device/comparator

- *The medical device under study (elastic adhesive tape):*

The MD is used in its indication: fixation.

(There is no detailed AE in the technical data sheet except for one contraindication: subjects sensitized to synthetic products).

Expected Incidents / AE:

- Intolerance to synthetic products
- Skin lesions and mucosal lesions in the path of fixation. (*13% of patients according to reference 7*)
- Loss of adhesiveness of the tape.

- *The medical device comparator (cord + sheath):*

The comparator is used in its indication: fixation.  
There are no AE detailed in the technical data sheet.

Expected Incidents / AE:

- Skin and mucosal lesions in the path of fixation (*43% of patients in reference 7*)
- Shearing, potential cut due to cord.

- List of expected AEs related to investigative procedures:

- *Medical device implementation:*

- Unscheduled extubations: self-extubations and accidental extubations during care (*7 to 16% of patients depending on reference 17*)
- Tracheal complications including laryngeal dyspnea
- Ventilator-associated pneumonia.

- List of expected AEs related to other additional procedures:

- *Auxiliary Drugs/MDs:*

- *Anti-adhesive (elastic adhesive tape group) to remove residual glue.*
- *Duoderm ® or other dressings used in curative treatment in case of lesions.*
- *Cavilon ™ type skin protection film.*

As these treatments are prescribed within the scope of their indications, any AEs for them are described in the respective summary of product characteristics (SPC)s, which serve as a reference.

-

*To the procedures performed, methods/techniques used for the purpose of the research:*

NA

- List of AEs related to the studied disease (death due to the disease, relapse, ...):

The patients included will be patients hospitalized in the intensive care unit, most often with multiple pathologies, who are intubated and put on invasive mechanical ventilation.

The potential complications of intensive care management of the study patients are identical to those expected in the non-study population, including, but not limited to, nosocomial infections, complications of intubation procedures, anesthesia drugs, consequences of prolonged bed rest, occurrence of shock with a risk of multi-visceral failure, and death.

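### Time to first lesion is counted from intubation although the device and its observation start at D0, and its end at extubation conflicts with recording to final extubation

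*Protocol*

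**What the plan says.** **Start of the window.** Section 2.2.1 sets the objective: "Compare the time to the first peri-oral lesion from intubation to extubation or D28". Section 2.2.2 defines the endpoint: "Time to the first peri-oral lesion from the time the patient is intubated until extubation". Section 6.2.1 (Secondary criteria) fixes the origin: "The time to onset will be calculated from the date of intubation to the date of first lesion onset". All three use intubation. Section 4.3 (Inclusion) sets the study clock elsewhere: "D0 is defined as the first day of the study fixation system of the ETT". The same section expects some patients to arrive with a tube already fixed by another method, which is then replaced by the study system. Section 3.3 bars patients transferred intubated from another ICU, and patients with a facial lesion on the fixation path on arrival.

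**End of the window.** Section 6.2.1 states: "Patients for whom no lesion appeared will be censored at the date of extubation or at the date of discharge from intensive care". Its third limit is D28, and a death censors on the day it occurs. Section 4.3 (Follow-up) states: "The follow-up by the nurse's notebook will stop at the final extubation". Its other limits are ICU discharge for a patient who leaves intubated, and D28. Extubations and re-intubations are recorded in the notebook, and re-intubations appear in the daily schedule.

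**Related time measures.** Section 6.2.1 gives the lesion rate as "number of patients with at least one lesion / total number of ventilator days". For patients with a lesion, the count of days ends at the first one. The Poisson models for self-extubation and tube repositioning use log intubation time as offset. The protocol defines neither measure of time.

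**The concern.** A time-to-event analysis should count a patient as at risk only while an event could happen and be seen. For a patient intubated before ICU arrival, neither holds between intubation and arrival. The tube is held by another system and no study observation takes place. Anyone who developed a lesion on the fixation path in that interval is not included. Every patient who is included therefore brings a stretch of time that cannot contain an event. Counting it as risk time lowers the apparent lesion rate and puts patients into early risk sets before they are under observation.

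At the other end, the observation rule distinguishes final extubation from extubation, and the censoring rule does not. An analyst must choose, and the choice is tied to an outcome of the trial: self-extubation is a secondary endpoint compared between arms. If the two systems hold the tube differently, the chosen reading removes or keeps different amounts of follow-up in each arm.

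One analysis also mixes two clocks, because the origin is intubation while the D28 limit belongs to the scale that starts at D0.

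**Working it through.** **The plan's own figure.** The protocol computes one figure, the sample size for the primary endpoint (section 6.2.2). Inputs: 35% and 20%, 90% power, alpha 5% (taken as two-sided), intra-class correlation 0.1, inter-class correlation 0.05, 16 centres, 24 patients per centre and period.

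- Individually randomised n per arm (unpooled variance): (1.960 + 1.282)² × (0.35 × 0.65 + 0.20 × 0.80) / 0.15² = 180.96
- Design effect: 1 + 23 × 0.1 − 24 × 0.05 = 2.1
- Total: 2 × 180.96 × 2.1 = 760. Solving for the cell size gives 23.4, rounded to 24, and 2 × 16 × 24 = 768.

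The 768 reproduces. It does not depend on the window for time to first lesion.

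**The start, case by case.**

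| Patient | Intubation to D0 |
|---|---|
| Intubated in the ICU | Gap small; origin and D0 nearly coincide |
| Intubated before ICU arrival, not from another ICU | Eligible; interval under another fixation, unobserved, event-free by the non-inclusion criterion |
| Intubated in another ICU and transferred | Not included |

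The mismatch sits in the second row. The protocol does not give the share of such patients or the length of the interval.

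**The end, reading by reading.** Take a patient who self-extubates on D2, is re-intubated, and has a first lesion on D6.

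- If *extubation* means the first one, section 2.2.2 closes the endpoint on D2. The patient is censored on D2, and the D6 lesion, observed under the device, is not used.
- If it means the final one, the patient has an event on D6. Unless the tube-free gap is removed, days without an oral tube count as risk time.

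Each reading is consistent with itself, but they give different data for the same patient. As a guide to how often this could arise, section 5.2.2 expects unplanned extubations (self-extubations and accidental ones during care) in "7 to 16% of patients depending on reference 17". That is 0.07 × 768 = 54 to 0.16 × 768 = 123 patients. How many would be re-intubated is not stated.

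**Illustrative size.** Assumptions that are not in the protocol: a constant lesion hazard over 10 device-days, reaching 35% with cord and 20% with tape.

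- Daily hazard, −ln(1 − p)/10: cord 0.04308, tape 0.02231, that is 43.1 and 22.3 per 1000 days; ratio 0.518.
- Mean device-days at risk, p/hazard: cord 8.12, tape 8.96.
- Rate when a fraction f of patients adds d off-device days: 1000 × p / (mean days + f × d).

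With f from 25% to 75% and d from 0.25 to 1 day, the cord rate falls to between 42.7 and 39.4 and the tape rate to between 22.2 and 20.6.

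| Extra off-device days per patient | Rate ratio, tape/cord |
|---|---|
| None | 0.518 |
| 0.5 in both arms | 0.521 |
| 1 in both arms | 0.523 |
| 2 in both arms | 0.528 |
| 1, tape only | 0.466 |
| 1, cord only | 0.582 |
| 2, tape only | 0.423 |
| 2, cord only | 0.646 |

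Off-device time shared equally lowers the absolute rates and barely moves the ratio. Only unequal time moves it materially.

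**The case against.** The strongest defence is that the effect is small and the text can be read sensibly. Each centre uses both systems in turn, so nothing stated suggests that time before D0 differs by arm, and the table shows that equal time hardly matters. Transfers from another ICU are already barred, and the fixation is systematically changed on arrival. The three statements of the origin agree with one another. The other limits in section 6.2.1, ICU discharge and D28, match those in section 4.3, so *extubation* is most naturally read as final. These points stand, and they limit the size. They do not remove the immortal time for patients intubated before arrival, and they leave the two wordings at the end unreconciled.

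A reader might infer two stronger claims, and the documents support neither.

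- **That risk time after re-intubation counts only when it contains a lesion.** This takes the first extubation for censoring and the final one for events. Section 2.2.2 bounds the endpoint itself at extubation, so under either consistent reading the asymmetry disappears. The patients with an unplanned extubation are therefore not a count of patients with biased risk time.
- **That the lesion rate counts ventilator days without an oral tube, for example after a tracheostomy during the stay.** Only tracheostomy on admission is a non-inclusion criterion, but no section says that such days enter the denominator. The term is undefined, and a definition may properly sit in the statistical analysis plan, which was not available.

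**Conclusion.** The time origin is wrong as written: a survival analysis from intubation without delayed entry counts unobserved, off-device, event-free time for patients intubated before ICU arrival. The end of the window is a conflict in wording between *extubation* (sections 2.2.1, 2.2.2 and 6.2.1) and *final extubation* (section 4.3), and it needs one answer because self-extubation is a compared outcome.

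The consequence is modest. Only secondary endpoints are touched. On the constant-hazard illustration, absolute rates fall by at most about 8% over the range examined for time before D0, and the between-arm ratio moves from 0.518 to no more than 0.528 when up to 2 extra days per patient are equal in both arms. Larger shifts (0.42 to 0.65) need up to 2 extra days per patient in one arm only, for which the protocol gives no evidence. All of these figures rest on assumed inputs.

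**What to change.** In sections 2.2.1, 2.2.2 and 6.2.1:

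- Start time to first lesion at D0, the first placement of the study fixation. Alternatively, keep intubation as the origin and let each patient enter the risk set at D0 (delayed entry).
- Censor lesion-free patients at final extubation, ICU discharge, death or D28, whichever comes first.
- Remove tube-free gaps between an extubation and a re-intubation from the risk time.
- Use the same D0-based oral-tube time as the denominator of the lesion rate and as the log-time offset for self-extubation and repositioning.

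The cost is low. Extubation and re-intubation are already recorded; a date for a tracheostomy during the stay might need a field. The rate would no longer be strictly per ventilator day, and the wording of a listed secondary endpoint would change in a trial already under way, so the change should be documented and dated before the comparative analysis. The sample size and the primary analysis do not change.
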